## Selection biases and confounders

### Cluster (Health Center) Level

The randomization of the clusters is particularly prone to biases due to the very low number. The main bias is that some catchment areas may have better access to services, may be more accessible for HTC or may have a different HIV-prevalence. In order to minimize this bias, health centers were matched based on their routine performance in terms of numbers accessing HTC per month, numbers testing positive per month and numbers enrolled into chronic HIV/AIDS care per month.

### Subcluster (village) level

Some campaigns may be conducted in communities that are particularly easy to access or that are particularly open to HTC-services. Other communities may have had a HTC-campaign just a few months ago. Some villages may be chosen because they are particularly suitable for one kind of intervention (door-to-door or pitso). In order to minimize these selection biases, the following procedure has been chosen: Before having been introduced of the kind of campaign (door-to-door or pitso) that will be conducted, the health center team provides a list of 10 villages that fulfill the eligibility criteria. From this list only 5 are randomly chosen (see subsection on selection of villages) for the campaigns.

### Individual level

On an individual level, the traditional way of HTC-campaigns (pitso) is a very biased approach as someone has to show up at the pitso in order to get the services. Door-to-door will probably reach other people as compared to pitso. However, it is part of the study-hypothesis that a different population will be reached using door to door. Differences in age and gender for example will be assessed as secondary outcomes. As the pitso is usually held in the center of the village (chief’s place), the door-to-door campaigns also start at the center and move towards the periphery.

## Study-flow

5 villages randomly chosen out of the 10 selected villages

5 villages randomly chosen out of the 10 selected villages

Campaigns are held according to the schedule.

# Ethical Considerations:

Selection of 10 villages per health center

6 Health Centers pitso

6 Health Centers door

Remaining outcomes are collected 5 weeks after campaigns were held

5 villages randomly chosen out of the 10 selected villages

## Facilities and teams conducting testing campaigns

All facilities involved are certified ART-centers where primary health care services, HTC and ART are provided according to the standards of the Ministry of Health and Social Welfare of Lesotho. The facilities work according to good practice of keeping patient’s intimacy and confidentiality. The teams are constituted of experienced lay-counselors and ART-nurses who practice HTC according to national standards.

## Informed consent

All patients will be approached for informed consent to use their data for analysis (see informed consent form annex 3). Only patients providing informed consent will be enrolled in the study. Patients refusing consent will benefit from the same services and quality of care as patients who agree in participation. In the case of children < 16 years, informed consent has to be provided by an adult care-taker. Persons may withdraw from the study at any moment without any diadvantages.

## Compensation

This study causes no any additional risk or cost to the patients. Therefore we do not pay compensation to the participants.

## Confidentiality

Confidentiality and privacy are ensured. The paper-records contain patient-names and are stored in a locked cupboard of the SolidarMed offices. The database containing the study variables is on a password-protected computer and the files are only accessible to the investigators and data managers. The database used for analysis will be anonymous, codes as unique identifier.

# Annex 1: Standards of procedures

**Standard Operation Procedures for HTC-campaigns**

- fill-in a file for each client approached for the provision of services
- follow the order of services provided as outlined below

| **Number** | Consecutive numbering. Each team starts every day at 1 |
| --- | --- |
| **Name** | Write Full Name |
| **Resident in CA?** | If the client is resident in the catchment area of the health center where the campaign takes place 🡪 tick Yes |
| **Blood Pressure** | Provide this service to all patients >18 years and write measured blood-pressure into the case. For children 🡪 leave empty.  If blood-pressure ≥140/90 mmHg 🡪 refer to health center for follow-up |
| **HTC accepted** | Propose HTC to all clients (independent of age) who are not already confirmed HIV-positive. All clients agreeing to HTC must fill out the national HTC-consent form!   - if client accepts HTC 🡪 tick “Yes” - if client does not accept HTC 🡪 tick “No” - if client states to be HIV-positive 🡪 tick “ICDP” - if it is a child < 12 years without her/his care-taker 🡪 tick “no guard” - if client is currently in the window-period (<3months since last HIV-test, as confirmed in bukana) 🡪 tick “window”   In case of children < 18 months with a positive HIV-antibody test, the care-taker must be counselled to seek care at the health center for a PCR-confirmation test. |
| **1^st^ time tester** | - if client states that he has never tested before 🡪 tick “Yes” - if client states that he once tested before 🡪 tick “No” - if client is not tested for any reason 🡪 tick “NA” |
| **Test result** | Copy result from test: Positive or Negative or Indeterminate  If the test is positive, the national HTC referral form must be filled out. A list of all newly patients tested positive must be provided to the health center. Patients who do not appear at the health center within 1 month must be traced by the health center (using the SolidarMed tracing fund) |
| **WHO-stage** | Stage all clients with a positive HIV-test according to WHO-staging (see annex) |
| **CD4-count** | Perform CD4-count (PIMA) to all clients who test HIV-positive and note the count in the field. |
| **Height/Weight** | Put height in cm and weight in kg |
| **Blood Glucose** | Provide blood-glucose testing to all patients > 18 years and write measured blood glucose into the case. For children 🡪 leave empty   - If blood-glucose ≥7mmol/l 🡪 refer to health center for follow-up - If blood-glucose ≥ 17mmol/l 🡪 transport to hospital immediately |
| **Deworming** | **Eligible for deworming:**  age 1-5 years and no documented deworming for the last 6 months   - If eligible and deworming supplied 🡪 tick Yes - If eligible and deworming refused by client 🡪 tick No - If not eligible 🡪 tick N/A |
| **Immunization** | **Eligible clients:**  Children or women of child-bearing age who are not vaccinated according to the national immunization-schedule   - If eligible and catch-up vaccination supplied 🡪 tick Yes - If eligible and catch-up vaccination refused by client 🡪 tick No - If not eligible 🡪 tick N/A |
| **Vitamin A** | **Eligible clients:**  Children or women of child-bearing age who have not received Vitamin A according to national schedule   - If eligible for Vitamin a and Vitamin A supplied 🡪 tick Yes - If eligible for Vitamin A but refused to take Vitamin A 🡪 tick No - If not eligible 🡪 tick N/A |
| **Uptake FP** | **Eligible clients:**  All women of child-bearing age.   - If eligible and accepted counselling for one FP-method (Pill, injection, coil) 🡪 refer to health center and tick Yes - If eligible but does not accept counselling for FP 🡪 tick No - If not eligible 🡪 tick N/A   All clients should receive condoms! However, for the study, distribution of condoms is not recorded as FP. If only condoms are given, but the women does not accept counselling for one of the following methods: Pill, injection or coil, then tick No. |

| **TB-screening** | TB-screening has to be done to all clients (HIV-negative and HIV-positive).  **Do screening as follows:**  **HIV-negative adult/adolescent person:**   - Are you coughing since more than 2 weeks? - Have you lost weight? - Do you have drenching/soaking sweats at night? - Do you have fevers?   🡪 if the answer of any of these questions is yes 🡪 tick TB-screening positive, assess the patient and provide 3 sputum bottles.  **HIV-negative infant/child:**   - Is the child coughing since more than 2 weeks? - Has the child unexplained fever for more than 3 days? - Does the child have failure to thrive/faltering growth or signs of severe malnutrition? - Has the child been in contact with someone with smear + TB?   🡪 if the answer of any of these questions is yes, tick screening positive, assess child for any danger signs and refer for MD-assessment.  **HIV-positive adult:**  Are you coughing?   - Have you lost weight? - Do you have drenching/soaking sweats at night? - Do you have fevers?   🡪 if the answer of any of these questions is yes, tick TB-screening positive, assess the patient and provide 3 sputum bottles.  **HIV-positive infant/child:**   - Is the child coughing? - Has the child fever? - Does the child have failure to thrive/faltering growth or signs of severe malnutrition? - Has the child been in contact with someone with smear + TB?   🡪 if the answer of any of these questions is yes, tick screening positive, assess child for any danger signs and refer for assessment by medical doctor at the hospital.  **Sputum-collection:**   1. Instruct TB-suspect on sputum collection 2. Fill out sputum request form 3. TB-suspect shall provide one on-the-spot sputum outside the house 4. TB-suspect shall bring the 3 bottles to the HC the following day 5. Note the clients in the TB-suspect register at the health center 6. Instruct health center to trace the TB-suspect, if he/she does not bring the sputum bottles within 5 days (the health centers can use the SolidarMed tracing fund) |
| --- | --- |
| **Sputum bottles given** | Provide 3 sputum bottles to each adult patient with positive TB-screening. If sputum-bottles provided 🡪 tick Yes. |
| **Informed consent** | All clients (no matter if they agree to HTC or not) have to fill out an informed consent.   - if they agree to provide their anonymous data for the study they shall tick “kea lumela/tekena” and either sign or provide finger-print - if they disagree to provide their anonymous data for the study they shall tick “Kea latola/tekena” |

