### Individuals

Individuals are excluded from the study if:

- Not fulfilling eligibility criteria

In addition individuals are excluded for the analysis of the primary outcomes if:

- Already known HIV-positive
- Prior HIV-test < 3 months (window-period)

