## Sample size

Expected difference in HTC-uptake between study-arms (1^st^ primary outcome): 80% (door-to-door) versus 65% (pitso)

k= 0.1

Power: 80%; Significance level: 5%

clients per cluster: 200 (persons attending the services per cluster)

According to formula of Hayes & Benett^[[2]](#footnote-2)^: 6 clusters per arm

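### Study consent is listed last in the field procedure, after HTC acceptance and test result, so entry to the primary-outcome denominators can depend on the outcome and may differ by arm

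*Protocol*

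**What the plan says.** **Order of steps.** Annex 1 of the Protocol (Standard Operation Procedures for HTC-campaigns) instructs staff to "follow the order of services provided as outlined below". The table begins with identification, residence and blood pressure. It goes on to HTC acceptance, first-time tester, test result, WHO stage and CD4 count, then the other services and TB screening. The last row is study consent: "All clients (no matter if they agree to HTC or not) have to fill out an informed consent".

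**Role of consent.** The Informed consent section says: "Only patients providing informed consent will be enrolled in the study". Under Eligibility criteria, Individuals, written consent is a condition of eligibility, and HTC refusers remain eligible provided they consent to the study. Neither section says when consent is taken.

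**Outcomes affected.** HTC acceptance is the first primary outcome and a new HIV-positive result is the second (Table 2). Only the first has a sample size, planned for "80% (door-to-door) versus 65% (pitso").

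**Recent tests.** Under Exclusion criteria, Individuals, the primary analysis leaves out anyone with "Prior HIV-test < 3 months (window-period"). In Annex 1, the HTC row allows the window code only for "<3months since last HIV-test, as confirmed in bukana". The same row accepts known HIV-positive status on the client's word.

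**The concern.** Uptake is the number of acceptors divided by acceptors plus refusers, counted among people who consent to the study. If consent is sought after the HTC decision, someone who has just refused a test can also decline the study and so leave the denominator. Someone who has just tested positive can do the same and leave the second and third primary outcomes. Staff seeking consent know the result and the arm.

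If refusers consent less often than acceptors, observed uptake is too high in both arms and the difference between them is distorted. If that gap is wider in one arm, a difference can be enlarged, reduced or produced by recruitment alone. An analysis restricted to consenters cannot correct this, because the information needed lies with those who are left out.

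The window rule raises a smaller, separate issue. A recent tester without the document can only be coded as accepting or refusing, and so stays in a denominator from which the exclusion criteria remove that person.

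**Working it through.** **1. Is the row order a working sequence?** The instruction to follow it suggests so. The TB-screening row supports this: its questions differ by HIV status, so for clients newly tested that day the HTC rows must be completed first. Nothing in the Protocol places study consent earlier.

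**2. The plan's own figure.** Inputs from Sample size: uptake 0.80 and 0.65, k = 0.1, "Power: 80%; Significance level: 5"% (taken as two-sided), and "clients per cluster: 200 (persons attending the services per cluster"). The unmatched Hayes and Bennett formula is

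c = 1 + (1.960 + 0.842)² × [p₁(1−p₁)/m + p₂(1−p₂)/m + k²(p₁² + p₂²)] / (p₁ − p₂)²

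- Bracket: 0.16/200 + 0.2275/200 + 0.01 × (0.64 + 0.4225) = 0.0008 + 0.0011 + 0.0106 = 0.01256
- c = 1 + 7.849 × 0.01256 / 0.0225 = 5.38, rounded up to 6

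The stated 6 clusters per arm is reproduced. Power with 6 is about 0.85.

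**3. Effect of consent that depends on HTC acceptance.** Let u be true uptake, a the study-consent rate among HTC acceptors and r the rate among refusers. Then

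observed uptake = u·a / [u·a + (1−u)·r]

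Neither a nor r is in the Protocol. Assume a = 0.95 throughout.

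Same r in both arms:

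| r | Door-to-door (u = 0.80) | Pitso (u = 0.65) | Difference | Power, 6 per arm |
|---|---|---|---|---|
| 0.95 | 80.0% | 65.0% | 15.0 | 0.85 |
| 0.90 | 0.76/0.94 = 80.9% | 0.6175/0.9325 = 66.2% | 14.6 | 0.82 |
| 0.70 | 0.76/0.90 = 84.4% | 0.6175/0.8625 = 71.6% | 12.9 | 0.68 |

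Power uses the formula in step 2 with m held at 200 and k at 0.1.

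Different r by arm, both directions:

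| r door-to-door | r pitso | Difference if truth is 80% v 65% | Difference if truth is 65% in both |
|---|---|---|---|
| 0.90 | 0.70 | 80.9 − 71.6 = 9.3 | 66.2 − 71.6 = −5.4 |
| 0.70 | 0.90 | 84.4 − 66.2 = 18.2 | 71.6 − 66.2 = +5.4 |

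When r = a in both arms the distortion is zero.

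**4. Window coding.** Suppose 5 unconfirmed recent testers join every 100 eligible pitso clients. If all 5 refuse, 65% becomes 65/105 = 61.9%. If they accept at 65%, the figure is (65 + 3.25)/105 = 65.0%, unchanged. The same coding rule applies in both arms, so the difference moves only if such clients are more frequent, or behave differently, in one arm.

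**The case against.** The instruction concerns services, and consent is not among the nine services listed under Campaigns. The table also holds fields such as number and name, so it could be read as form layout, and consent is an eligibility criterion in any case. That leaves some room for doubt, but no passage sets an earlier time, and a reader following Annex 1 would take consent last.

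The likely bias may be small. Consent covers only the use of anonymous data, services are the same either way, and HTC refusers are expressly asked and kept eligible. The absolute number accepting HTC, also part of the first primary outcome, does not depend on whether refusers consent. These points stand. They limit the size without removing the mechanism, and 90% consent among refusers costs under half a point.

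A reader might go further and infer that the denominator does depend on outcome and arm. The Protocol has no data on this. A reader might also suppose that the bukana is easier to produce at home than at a pitso. The Protocol does not say where it is kept, and the opposite is arguable: the campaign is announced 4 to 7 days ahead and offers services that rely on records. Nor is there text to show that people who leave after the health talk go unrecorded.

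The remedy is also imperfect. Someone intending to refuse HTC can decline the study beforehand too, and a research form signed first might affect uptake.

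**Conclusion.** The concern holds as a risk that the procedure opens. Consent decides entry to the analysis and, on the natural reading of Annex 1, is taken after the first two primary outcomes are known. The uptake and positivity denominators can therefore depend on the outcome and may differ by arm.

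Size and direction are unknown. On assumed consent rates, equal selection in both arms reduces the planned 15 points to between about 14.6 and 13. Unequal selection between arms can move the difference up or down. Scenarios in which only pitso refusers withhold consent, shrinking the difference sharply, are one-sided: the mirror case enlarges it, and the Protocol favours neither.

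Separately, the exclusion criteria and Annex 1 define a recent test differently. That inconsistency needs no assumption about the arms, but an arm-specific bias from it is not supported by the text.

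**What to change.** - Move the study-consent row of Annex 1 ahead of the HTC-acceptance row, and state that timing in the Informed consent section.
- Report by arm and cluster, as nameless counts, the number of clients approached, HTC yes/no and study consent yes/no. Annex 1 already requires a file for each client approached and a signed agreement or refusal, so this is mainly tabulation. It also shows any selection that remains after the reordering.
- Reconcile the recent-test wording in the exclusion criteria and Annex 1. Add a code for a recent test that is stated but not confirmed, and analyse the primary outcome with and without these clients. Excluding every self-report outright is not advised, because it would give a reluctant client a way out of the denominator.

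The cost is a few minutes before the HTC offer and one extra tick box. The service package is unchanged.

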# Annex 2: Study-questionnaire (data-collection tool)

| **Number** | **Name** | **Resident in CA?** | | **Sex** | | **Age** | **BP** |
| --- | --- | --- | --- | --- | --- | --- | --- |
|  |  | ⬜ Y | ⬜ N | ⬜ F | ⬜ M |  | mm/Hg |

| **HTC accepted** | | | | | | | **1st time tester** | | | | **Test Result** | | | |
| --- | --- | --- | --- | --- | --- | --- | --- | --- | --- | --- | --- | --- | --- | --- |
| ⬜Y | ⬜ N | | ⬜ ICDP | ⬜ no guard | | ⬜ window | ⬜ Y | ⬜ N | | ⬜ N/A | ⬜ Pos | ⬜ Neg | | ⬜ Ind |
|  | |  | | |  |  |  | |  | |  |  | |  |
| **WHO-stage** | | | | | **CD4** | | **TB-screening** | | | | **Sputum bottles given** | | | |
|  | | | | | cells | | ⬜ pos | | ⬜ neg | | ⬜ N | | ⬜ Y | |

| **Height** | | | | **Weight** | | | | **Blood-glucose** | | | | |
| --- | --- | --- | --- | --- | --- | --- | --- | --- | --- | --- | --- | --- |
| cm | | | | kg | | | | mmHg | | | | |
|  | | |  | | |  | | | |  | | |
| **Deworming** | | | **Immunization** | | | **Vitamin A** | | | | **Take-up FP** | | |
| ⬜ Y | ⬜ N | ⬜ N/A | ⬜ Y | ⬜ N | ⬜ N/A | ⬜ Y | ⬜ N | | ⬜ N/A | ⬜ Y | ⬜ N | ⬜ N/A |

**Outcomes (leave empty, except if already registered icdp)**

| **Brought sputum** | | **Sputum-result** | | **Enrolled on pre-ART** | | **Enrolled on ART** | | **Pre-ART** | **ART-Nb** |
| --- | --- | --- | --- | --- | --- | --- | --- | --- | --- |
| ⬜ Y | ⬜ N | ⬜ Neg | ⬜ Pos | ⬜ Y | ⬜ N | ⬜ Y | ⬜ N |  |  |
